### Statistical analysis

The statistical analysis will be carried out at the level of candidate gene/region, higher dimensional epigenetic states and epigenome-wide association, using Stata (V.17 or later), Python and R. The observational study will be analysed using applied regression models (eg, multiple linear regression, logistic regression, multilevel modelling, with adjustment for relevant covariates). The intervention studies will be analysed in terms of intention to treat and, for the nutritional interventions, the response to the actual change in nutritional status. Monte Carlo methods and simulation will be used. Dimension reduction techniques, such as principal component analysis, will be applied to high-dimensional genomic data to reduce the number of variables to those containing the essential information for use in the regression models. Epigenetic ‘type’ describes summary measures of epigenetic states in individuals derived from PCA for example. The focus of the statistical analysis is set out in box 2.

Box 2Focus of the epigenetic work within the UKRI GCRF Action Against Stunting HubFocus of the epigenetic work:Epigenetic states characteristic of stunting and related outcomes such as cognitive development.Epigenetic states in non-stunted children from populations subject to stunting.The effect of exposures (nutrition–microbiome–gut health–parasites–pathogens–hygiene–emotional stress–home environment) in the first 1000 days of life on epigenetic states in children and risk of stunting.The effect of parental epigenome on offspring epigenetics and risk of stunting.The effect of parental life history and exposures at their birth and early childhood and at the time of the current pregnancy (season, food availability, nutritional status, physical activity) on parental epigenetic states.The effect of interventions (egg, synbiotic) on epigenetic state.The effect of baseline epigenetic type on the ability to respond to interventions.Comparison of the above between countries/ethnicities/populations.The link between epigenetics and the wider project thematic areas (nutrition–microbiome–gut health–parasites–pathogens–hygiene–emotional stress–home environment).

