**Figure 1 F1:**
[figure not shown]
Design of observational epigenetic study.

The intervention studies differ between the research centres and the primary outcomes of interest, but all will include epigenetic assessments. In Indonesia, an egg supplementation study (3 boiled eggs per week) will be carried out in n=153 women during pregnancy with n=153 controls. In India, egg supplementation (1 egg per day) will be carried out in n=350 (intervention on n=70) children (An open-label randomised controlled trial on the impact of an egg intervention on infant linear growth and cognition in Hyderabad, India: a UKRI GCRF Action Against Stunting Hub protocol paper. *BMJ Paeds Open, Kumar Banjara et al (in press*)). In Senegal, the objectives are to recruit n=236 children to receive a synbiotic with n=472 children as controls (Improving gut health and growth in early life: a protocol for an individually randomised, two-arm, open-label, controlled trial of a synbiotic in infants in Kaffrine District, Senegal. *BMJ Paeds Open, Kadia et al (in press*)). In each case, the local observational cohorts are used as controls and the epigenetic comparisons in the intervention studies are illustrated in figure 2.

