**Figure 2 F2:**
[figure not shown]
Design of intervention epigenetic study. *Some epigenetic variables are used as covariates for adjustment as relevant to intervention.

In both the observational and the intervention studies, measurements of DNA methylation will be carried out in saliva samples from children collected within 1 month of birth and at 18 months of age, and from mothers and fathers around the time of birth. Anthropometry and other outcomes measures will continue to 24 months. The target is to collect the parental saliva samples within 1 month of delivery but in some cases, particularly for the fathers, this may be delayed for practical reasons and the timing of saliva sampling will be recorded. Saliva has been chosen to facilitate the easy and non-invasive collection of samples from babies and young children under potentially challenging field conditions and because saliva would be suitable for the development of epigenetic field tests of stunting risk. Samples will be collected from children in the first month postnatally using ORAcollect for Pediatrics OC-175 kits and at 18 months of age using Oragene DNA OG-675 kits. Samples will also be collected from mothers and fathers around the time of birth using Oragene DNA OG-600 kits (DNA Genotek, Ottawa, Canada). The kits include instructions for sample collection and they allow quick stabilisation of the DNA. The genomic DNA extraction will be performed using DNA Genotek Oragene prepIT.L2P reagent, according to the manufacturer’s protocol (DNA Genotek, Ottawa, Canada). For epigenetic methods requiring bisulphite conversion of DNA, the Zymo EZ DNA Methylation-Gold Bisulfite kit (Zymo Research, California, USA) will be used.

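### In Indonesia no maternal or newborn methylation sample precedes the eggs, so the baseline-type analysis of response cannot be done there as listed

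*Protocol article*

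**What the plan says.** All references are to the protocol article.

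- **Timing of the intervention** (Methods and analysis, text after Figure 1). In Indonesia, "an egg supplementation study (3 boiled eggs per week) will be carried out in n=153 women during pregnancy with n=153 controls". In India and Senegal the participants who receive the intervention are children.
- **Timing of methylation sampling** (Methods and analysis, text after Figure 2). One schedule covers everything: "In both the observational and the intervention studies, measurements of DNA methylation will be carried out in saliva samples". The samples come from "children collected within 1 month of birth and at 18 months of age, and from mothers and fathers around the time of birth". For parents, "The target is to collect the parental saliva samples within 1 month of delivery but in some cases" this may slip, fathers being the main example. No earlier sample is described for any family member, and no exception is made for Indonesia.
- **Planned use** (Statistical analysis, Box 2). One item is "The effect of baseline epigenetic type on the ability to respond to interventions". The item before it is the effect of the egg and synbiotic interventions on epigenetic state. The item after it is comparison of the preceding items across countries and populations.
- **Adjustment** (Figure 2 legend). "Some epigenetic variables are used as covariates for adjustment as relevant to intervention".

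**The concern.** A modifier of response has to be measured before treatment starts, or at least be something treatment cannot change. Otherwise participants with the same value in the two arms are no longer comparable: a given newborn methylation level reached with eggs is not the same starting point as that level reached without them. A treatment-by-type interaction built on such a measure mixes what the eggs did to methylation with who benefits from eggs.

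Box 1 gives prediction of response from epigenetic type as a practical aim. An Indonesian result that looks like prediction but rests on a post-treatment measure could be carried into that aim and into the country comparison. The same measure used as an adjustment covariate would remove any part of the egg effect that passes through methylation, and could create an effect where there is none.

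**Working it through.** **1. Order of events**

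| Study | Who is treated, and when | First maternal or child methylation sample | Can that sample be a baseline? |
|---|---|---|---|
| Indonesia | Women, during pregnancy | Mother around birth; child within 1 month of birth | No |
| India | Children; starting age not given in this article | Child within 1 month of birth | Yes, if taken before the first dose |
| Senegal | Children; starting age not given in this article | Child within 1 month of birth | Yes, if taken before the first dose |

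Reading the parental timing to include a sample shortly before delivery does not change the Indonesian row, because supplementation in pregnancy has already begun. The father's sample is also late, but eggs eaten by the mother would not plausibly alter it.

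**2. Consistency within Box 2.** One item treats methylation as an outcome of the eggs; the next treats baseline type as a predictor of response to interventions. In Indonesia only the after-treatment maternal and newborn measures are available, and they cannot serve as both.

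**3. The plan's own figure.** The Statistical power section gives 153 per group for 80% power, a 3% difference, SD 6% and 100 Bonferroni-adjusted tests. Taking an overall 0.05 and two-sided tests (assumed, not stated): d = 3/6 = 0.5 and alpha = 0.05/100 = 0.0005. The normal formula gives n = 2(3.481 + 0.842)²/0.5² = 149.5, so 150. The exact t-test gives 152.5, so 153, with power 0.802 at 153. The figure reproduces. It was derived for stunted versus non-stunted children; the same number is the Indonesian group size.

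**4. What conditioning on the birth sample could do.** The inputs below are assumptions, except that the egg effect on birth methylation is set at the plan's 0.5 SD.

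*(a) Mediation.* Let M = 0.5A + u and Y = cA + bM + e, where A is the egg arm. The total effect is c + 0.5b; adjusting for M leaves c, so 0.5b is removed.

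| b (SD of outcome per SD of M) | Removed, 0.5b | Share of a 0.5 SD total effect | Share of a 0.3 SD total effect |
|---|---|---|---|
| 0.2 | 0.10 | 20% | 33% |
| 0.4 | 0.20 | 40% | 67% |
| 0.6 | 0.30 | 60% | 100% |

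*(b) Common cause.* Let the eggs have no effect on the outcome, and let an unmeasured U affect both M and Y with coefficient g. Among participants with the same M, the arms differ in U by −0.5g, so the estimated egg effect is −0.5g² instead of 0.

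| g | Difference in U at equal M | Bias, −0.5g² (SD) | Actual type I error at nominal 5%, 153 per group (4,000 simulations) |
|---|---|---|---|
| 0.3 | −0.15 | −0.045 | about 7% |
| 0.5 | −0.25 | −0.125 | about 19% |
| 0.7 | −0.35 | −0.245 | about 66% |

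The second column is the loss of comparability within levels of M that undermines the modifier analysis. The last two columns apply to an analysis that adjusts for M. Bias in the interaction itself is not sized here; it depends on how the egg effect on M varies between participants.

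*(c) Power if half of a 0.5 SD effect is adjusted away (d = 0.25).* With 153 per group the noncentrality is 0.25 × √(153/2) = 2.19. The number of tests matters, because the Statistical power section says it will be reduced for intervention studies.

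| Tests | Two-sided alpha | Power at d = 0.5 | Power at d = 0.25 |
|---|---|---|---|
| 100 | 0.0005 | 0.80 | 0.09 |
| 10 | 0.005 | 0.94 | 0.26 |
| 1 | 0.05 | 0.99 | 0.59 |

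These are exact t-test values and ignore any gain in precision from adjustment.

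**The case against.** The best defence is that Box 2 is a list for the whole Hub and assigns no item to a country. The baseline-type item could be met by India and Senegal alone, and a condensed article need not say so. The text also plans intention-to-treat analysis, and defers the models to each publication. This lowers the weight of the point but does not remove it. Nothing in the article restricts the item, the next item carries it into a country comparison, and the sampling schedule is expressly common to all studies. No later choice of model can turn a sample taken around birth into one taken before the eggs.

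A reader might go further and infer that the Indonesian intention-to-treat effect will be biased because epigenetic covariates are adjusted for. The article does not support that. Only the Figure 2 legend could be read here, not the figure, and it says that some variables are used, chosen by relevance to the intervention. Nothing in the text names maternal or newborn methylation as a covariate in Indonesia, and paternal methylation would be harmless there.

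A reader might also infer a fall in power from 80% to about 9%. That needs half of the effect to be mediated, which is assumed, and 100 tests, which the article does not fix for the intervention studies. With fewer tests the loss is smaller, as the table shows.

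Nor does the point call for barring every covariate recorded after supplementation starts, or for moving the maternal sample to recruitment. Moving it would lose the maternal outcome after the intervention and, unless the controls' samples moved too, break comparability with them.

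**Conclusion.** The point holds for maternal and newborn methylation in Indonesia. On the stated schedule neither is a baseline for the egg intervention, so the Box 2 analysis of baseline type and response cannot be delivered there, and running it with the birth samples would condition on a post-treatment variable. This rests only on the stated timing and needs no numerical assumption.

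The adjustment part is conditional: it applies only if Figure 2 or the analysis plan uses maternal or newborn methylation as a covariate in Indonesia. The size of any bias cannot be taken from the article. The figures above (20% to 100% of an effect removed, or type I error of 7% to 66%) show how it varies with assumed inputs and are not estimates for this study. India and Senegal are unaffected wherever the saliva sample precedes treatment.

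**What to change.** - In Box 2 and the analysis plan, limit the baseline-type objective and its country comparison to studies and participants whose saliva sample is dated before the first intervention dose. In India and Senegal, check this participant by participant.
- For Indonesia, label maternal and newborn methylation as post-intervention measures. Analyse them as outcomes, or as mediators in an analysis declared as mediation.
- If Figure 2 lists either as an adjustment covariate for Indonesia, remove it from the intention-to-treat analysis. Paternal methylation, child age at sampling, sampling time, and technical or cell-type adjustment of methylation outcomes may stay.

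The cost is wording and a date check. The downside is that one Box 2 objective is dropped for Indonesia.

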### Statistical power

The statistical power depends on the structure of the data (eg, covariance in methylation signatures^6^), the statistical approach and the epigenetic hypothesis. An approximate estimate can be derived for a simple comparison of epigenetic states in stunted and non-stunted children. For that comparison, the study would have a power of 80% to test 100 independent epigenetic hypotheses (p value Bonferroni adjusted for multiple testing) with 153 subjects in each group; based on a modest effect on methylation of 3% and the population standard deviation (6%) we observe using the same methodologies in other groups. For the intervention studies and subanalyses, the power may be reduced depending on the precise analysis and the number of hypotheses will be reduced accordingly. The statistical power for each analysis will be specified in publications along with the mathematical models. In addition, the data will be made available to others to allow them to generate and test their own hypotheses.

The strategy of random population sampling of n=500 is estimated to yield 150–200 stunted children, based on the estimated prevalence of stunting in the target populations (30%–40%). The national prevalence of stunting at the national level in Indonesia is 31% (Ministry of Health Republic of Indonesia. National Report of Basic Health Survey: 2018. Jakarta: National Institute of Health Research and Development; 2019 (accessed Oct 11 2021). Available from: http://labdata.litbang.kemkes.go.id/images/download/laporan/RKD/2018/Laporan_Nasional_RKD2018_FINAL.pdf) and 44% in the East Lombok District study location (Ministry of Health Republic of Indonesia. West Nusa Tenggara Province Report of Basic Health Survey: 2018. Jakarta: National Institute of Health Research and Development; 2019 https://drive.google.com/file/d/1vAcl4htxwKfKTqgRxaigCb16k3FjrnNv/view (accessed Oct 11 2021)). The prevalence of stunting in India has been on a downward trend for the past two decades but nationally in 2017, it remained high at 39% and the prevalence in the study location in Hyderabad—an urban slum—is estimated to be 61% at 18 months and 27% at 24 months of age.^27^ The rate of stunting in Senegal was approximately 26% in 2017 (Senegalese Ministry of Health National report of Continuous Demographic Health Survey (DHS-Continuous) 2017 https://www.ansd.sn (accessed 14 Feb 2022)).

### Patient and public involvement

Detailed information on participant and public involvement is presented in other protocols in this series. It involves the participation of lay members on ethical review committees and public engagement activities to publicise the research. A workstream on shared values is designed to understand the perspective of local populations affected by stunting and their views. These activities and conversations have informed the development of the research and plans for dissemination and follow-on activities.

### Dissemination

The data will be published in a range of discipline specific, cross-disciplinary, and general, peer-reviewed journals. The findings will also be translated into recommendations for policy geared towards preventing the incidence and reducing the negative impacts of childhood stunting that can be used by international organisations and governments. This will include the development of a Decision Support Tool for policy-makers based on the insights produced in the course of this work. The genomic data will be posted in public repositories such as the European Nucleotide Archive or the Gene Expression Omnibus (GEO) or equivalent repository, or as required by the relevant journal reporting the findings. Hub data will also be made available with a preference for minimal licence restrictions (typically CC-BY CC-BY-NC CC-BY-ND) as per UKRI guidance, after assessment for exploitation potential. In some cases, it may be necessary to obtain agreement on data use prior to release because of ethical or other considerations.

### Ethics

This study involves human participants. The study was approved by the relevant ethical committees in Indonesia (The Ethical Committee from Faculty of Medicine Universitas Indonesia; ND-855/UN2.F1/ETIK/PPM.00.02/2020), India (National Institute of Nutrition (ICMR), Ministry of Health and Family Welfare, Government of India, CR/04/I/2021, 01-11-2018; renewed 16-07-2021) and Senegal (The National Ethic Committee for Health Research; SN1978.31/12/2019). The study has also been approved by the Institutional Ethics Committee of the London School of Hygiene and Tropical Medicine (approval number 17915). Participants gave informed consent to participate in the study before taking part.
